Within this multidimensional approach, mental health constitutes a central component of postpartum health. It represents a major clinical and public health concern, with potential consequences for parents, infants and family functioning.^9 10^ Depression and anxiety affect a substantial proportion of mothers and co-parents,^9^,^11^ and some develop childbirth-related post-traumatic stress disorder (CB-PTSD), a subtype of PTSD with specific perinatal triggers.^12^,^14^ In Switzerland, a monocentric study with a small convenience sample reported that 20.7% of mothers and 7.2% of fathers met criteria for probable PTSD 1 month post partum.^15^ Although the study relied on a general PTSD screening tool and was affected by selection bias, it highlighted the potential magnitude of trauma symptoms and the clinical relevance of avoidance behaviours. Yet, long-term support remains limited, and trajectories of recovery are rarely monitored, despite their known consequences on quality of life.^3 16^ Avoidance and disengagement from care, recognised as key features of CB-PTSD, may also compromise help-seeking and widen existing gaps in support.

The quality and experience of care during childbirth and the postpartum period represent another key component of this framework, as they may shape health trajectories across multiple domains.^7 17^ According to the WHO, high-quality maternity care should be safe, effective, timely, equitable and people-centred and should integrate both provision and experience of care.^7 8^ Clinical practices during childbirth, such as labour induction, episiotomy, caesarean delivery or limited access to pain relief, have been associated with trauma, dissatisfaction and poor mental health outcomes.^18^ In Switzerland, postpartum follow-up includes an average of 7.9 home visits per mother, one of the highest rates in Europe.^19^ However, little is known about how the content and perceived quality of this care relate to health trajectories after childbirth. Despite growing attention to respectful maternity care, few population-based studies investigate how care provision and care experiences relate to long-term postpartum recovery, particularly in interaction with mental health, physical recovery and broader social determinants.^2 17^

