### Data collection

Data are collected from four complementary sources: (1) obstetric and neonatal clinical data from medical records, (2) self-administered online parental questionnaires, (3) a structured institutional survey completed by participating centres and (4) linkage with national hospital discharge datasets (Medical Statistics of Swiss Hospitals, which also include data from birth centres). Clinical data are recorded at baseline and include maternal medical and obstetrical history, pregnancy characteristics and complications, labour and childbirth management (eg, induction, analgesia, mode of childbirth), postpartum complications (eg, haemorrhage, infection), and neonatal outcomes such as Apgar score, birth weight and neonatal unit admission. Participants are invited to complete four online questionnaires, shortly after birth (baseline), and at 2, 6 and 12 months post partum. All questionnaires are provided in French, German, Italian and English. In parallel, a methodological collaboration was established with the Swiss-Peristat project (SNSF 222882), which aims to validate national perinatal care quality indicators. A subset of clinical data collected in SOCRATES will be used to estimate the accuracy of routinely collected hospital administrative data from the Swiss Federal Statistical Office.

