### Outcome measures and instruments

Primary and secondary outcomes are measured using validated self-report instruments. The full list of instruments, respondents, domains and time points is detailed in table 1.

**Table 1 T1:** Domains, validated instruments and timing of data collection for mothers and co-parents in the SOCRATES cohort

Domain	Topic	Validated scale	Number of items	Respondents and time points				Ref.
				Childbirth	2 months	6 months	12 months	
Childbirth	Fear of childbirth	Fear of Childbirth Visual Analogue Scale (FOCP-VAS)	1	◯	/	/	/	^54^
	Childbirth experience	Questionnaire for Assessing Childbirth Experience (QACE SF)	5	◉	/	/	/	^48^
	Traumatic experience	Peritraumatic Dissociative Experiences Questionnaire (PDEQ)	10	◉	/	/	/	^49^
	Satisfaction with care	Behaviour of the Mother’s Caregivers–Satisfaction Questionnaire (BMC-SQ)	7	◯	/	/	/	^50^
Physical health	General health	Minimum European Health Module (MEHM)	1	◉	/	/	/	^55^
		EuroQol Visual Analogue Scale (EQ-VAS)	1	◉	◉	◉	◉	^45^
	Early recovery	Obstetric Quality of Recovery-10 (ObsQoR-10)	10	◯	/	/	/	^56^
	Fatigue	Fatigue Assessment Scale (FAS), short selection at 6 and 12 months	10	/	◉	◉	◉	^38^
	Urinary incontinence	International Consultation on Incontinence Questionnaire–Urinary Incontinence (ICIQ-UI)	3	/	◯	◯	◯	^40^
	Anal incontinence	Jorge and Wexner anal incontinence score	3	/	◯	◯	◯	^41^
	Pain	Pain Intensity derived from the Brief Pain Inventory (BPI)	1	◯	◯	◯	◯	^39^
	Premenstrual symptoms	Premenstrual Symptoms Screening Tool (PSST)	1	◯	/	/	/	^57^
	Pelvic floor symptoms	Pelvic Organ Prolapse Distress Inventory-6 (PoPDI-6)	3	/	/	/	◯	^58^
Quality of life	Quality of life	EuroQol 5-Dimension 5-Level (EQ-5D-5L)	5	◉	◉	◉	◉	^45^
	Satisfaction With Life	Satisfaction With Life Scale (SWLS)	5	◉	/	/	◉	^59^
	Well-Being	The WHO–Five Well-Being Index (WHO-5 well-being)	5	◉	◉	◉	◉	^46^
	Flourishing	Secure Flourishing Index	12	/	/	/	◉	^60^
Mental health	Post-traumatic stress disorder (PTSD)	City Birth Trauma Scale for mothers/for partners (CB-PTSD)	29/29	/	◉	/	/	^25^ ^30^
	Depression, anxiety	Edinburgh Postnatal Depression Scale (EPDS and EPDS-3A)	10	◉	◉	◉	◉	^61^
	Stress	Perceived Stress Scale-4 (PSS-4)	4	◉	◉	◉	◉	^62^
	Loneliness	UCLA-Loneliness Scale-3 (UCLA-3)	3	◉	◉	◉	◉	^63^
	Resilience	Brief Resilience Coping Scale (BRCS)	4	◉	/	/	/	^64^
	Suicidal ideation	Patient Health Questionnaire-9 (PHQ-9) – item 9	1	◉	◉	◉	◉	^65^
Sexual health	Sexual function	Female Sexual Function-6 (FSFI-6)	6	/	/	◉	◉	^42^

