	Sexual well-being	Natsal Sexual Well-being measure (NATSAL SW)	13	/	/	/	◉	^44^
Parenting	Bonding	Mother-to-Infant Bonding Scale (MIBS)	8	/	◉	/	/	^66^
	Parenting confidence	Me as a Parent Scale (MaaPs-SF)	4	/	◉	◉	◉	^67^
	Relationship	Brief Coparenting Relationship Scale (B-CRS)	14	/	/	◉	/	^68^
Support	Couple satisfaction	Couple Satisfaction Index (CSI-4)	4	◉	◉	◉	◉	^69^
	Social support	Multidimensional Scale of Perceived Social support (MSPSS)	12	◉	◉	◉	◉	^70^
Lifestyle	Sleep quality	Pittsburgh Sleep Quality Index (PSQI)	1	◉	◉	◉	◉	^71^
	Sleep	Insomnia Severity Index (ISI-3)	3	◉	◉	◉	◉	^72^
	Eating and body image	Maternal Body Image and Eating Behaviours Scale (MBIEB-S), short selection	4	/	◯	◯	◯	^73^
	Body image	Maternal Postpartum Quality of Life (MAPP-QOL)	1	/	◯	◯	◯	^74^
	Physical Activity	International Physical Activity Questionnaire (IPAQ short form)	2	◉	◉	◉	◉	^75^
	Physical Activity	Global physical activity questionnaire (GPAQ)	1	◉	◉	◉	◉	^76^
Work	Work-Family Conflict	Work-Family Conflict Scale (ISSP)	4	/	•	◉	◉	^77^

◯: mother; •: co-parent; ◉: Both mother and co-parent.

SOCRATES, Stress Of Co-parents Related to A Traumatic Experience of birth across Switzerland.

To address the primary objective (1), the prevalence and severity of CB-PTSD at 2 months post partum is measured using the City Birth Trauma Scale.^25^ This 29-item instrument, aligned with DSM-5 criteria, demonstrated excellent internal consistency and test–retest reliability in postpartum samples.^26 27^ A version specifically adapted for co-parents is used where applicable, featuring slightly modified wording to reflect their non-birthing role while preserving the instrument’s conceptual structure and psychometric properties.^28^,^31^

To address objective (2), depression and anxiety symptoms are assessed from the perinatal period to 12 months using the Edinburgh Postnatal Depression Scale (EPDS).^32^ This 10-item screening tool provides good internal consistency, is widely used in postpartum populations and validated in all four languages.^33 34^ In addition to the total score, anxiety symptoms are explored using the EPDS-3A subscale, which comprises items 3, 4 and 5, and has been proposed as a brief indicator of postnatal anxiety.^35^ Suicidal ideation is assessed using the ninth item of the Patient Health Questionnaire-9.^36^

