### Statistical analysis and weighing procedure

Descriptive analyses will be conducted to summarise participants’ characteristics and outcomes. Associations between predictors and outcomes will be examined using multivariable regression models, accounting for potential confounders identified through literature review, clinical expertise and directed acyclic graphs. Sensitivity analyses will be performed to evaluate the robustness of the findings. Missing items will be imputed using standard procedures whenever relevant (eg, multivariate imputation by chained equations). All analyses will be carried out using statistical software such as R or Stata.

To ensure representativeness at the national level, we will apply a weighting procedure that includes the following steps. First, base design weights are computed to account for differences in participation across maternity care institutions. Second, raking is applied to align the weighted sample distribution with known population margins, using key sociodemographic variables (education, income, age, Swiss nationality and parity). Predictive models (eg, Random Forest, XGBoost, Support Vector Machines) are employed to impute missing values in these key variables before calibration. Third, non-response adjustment weights are estimated through logistic regression using region, parental origin, education, ethnicity, age, living conditions, institution type and number of pregnancies as predictors. Predicted response probabilities from this model are then used to construct inverse probability weights, such that respondents with a lower predicted probability of response receive larger weights. To prevent undue influence of extreme weights, trimming is applied at predefined thresholds. The final adjusted weights are then assigned to all observations for subsequent analyses.

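### The non-response weights behind the 2-month CB-PTSD prevalence use no symptom or birth-experience data, although the protocol names avoidance as a key feature of the disorder

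*Protocol article*

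**What the plan says.** All references are to the protocol article.

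- **Outcome.** Under Outcome measures and instruments, "the prevalence and severity of CB-PTSD at 2 months post partum is measured using the City Birth Trauma Scale". Table 1 schedules this scale for both parents at 2 months and at no other wave.
- **Non-response.** Under Statistical analysis and weighing procedure, base weights are followed by raking to education, income, age, nationality and parity. A logistic response model is then fitted "using region, parental origin, education, ethnicity, age, living conditions, institution type and number of pregnancies as predictors", and "Predicted response probabilities from this model are then used to construct inverse probability weights". The Abstract says that the weighting is meant to deal with attrition.
- **Other tools in the same section.** Chained-equation imputation is mentioned for missing items. Sensitivity analyses are promised without content.
- **Link between disorder and disengagement.** The Introduction states: "Avoidance and disengagement from care, recognised as key features of CB-PTSD, may also compromise help-seeking".
- **Symptom data available.** Under Data collection, "Participants are invited to complete four online questionnaires, shortly after birth (baseline), and at 2, 6 and 12 months post partum". Table 1 gives EPDS (with EPDS-3A), PSS-4 and WHO-5 to both parents at all four waves, and PDEQ and QACE to both parents at baseline.

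**The concern.** Neither the raking margins nor the response-model predictors include a symptom or birth-experience measure. Weighting on them makes responders resemble the target population in background and setting. It does nothing about a parent who skips a 29-item birth-trauma questionnaire because of trauma symptoms, except so far as those symptoms follow the listed variables.

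The protocol itself gives a reason to take this seriously, because it describes avoidance as part of the condition being counted. If the same avoidance keeps some parents from answering, the national prevalence is too low. The confidence interval would not show it, since it reflects sampling error only. The study also holds data that could test the assumption, yet the article assigns them no role in the primary estimate.

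**Working it through.** **1. Inputs.** From Sample size and power calculation: assumed prevalence 5%, 95% CI, margin ±1 point, 1900 complete responses, 60% follow-up, target about 3200. From Recruitment and participation: 2785 mothers consented to questionnaires and 2337 started the baseline one. The documents give neither the CB-PTSD prevalence in non-responders nor the number who return after missing 2 months. Both are assumed below.

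**2. The plan's own figure.** n = z²p(1−p)/d².
- z = 1.96: 3.8416 × 0.05 × 0.95 / 0.0001 ≈ 1825.
- z rounded to 2: 4 × 0.0475 / 0.0001 = 1900, the stated figure.
- 1900 / 0.60 = 3167, stated as about 3200.

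**3. Sampling margin.** 1.96 × √(0.0475/n) is 0.98 points at n = 1900. At 60% of 2785 (n = 1671) it is 1.04 points.

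**4. Bias if response depends on symptoms.** Let r be the response proportion, p the prevalence in responders and q that in non-responders, and suppose the weights explain none of the difference. The true value is rp + (1−r)q, so the shortfall is (1−r)(q−p).
- q = 7.5%: 0.6 × 5% + 0.4 × 7.5% = 6.0%, so 1.0 point too low. Odds ratio (0.075/0.925)/(0.05/0.95) = 1.54.
- q = 10%: 0.6 × 5% + 0.4 × 10% = 7.0%, so 2.0 points too low. Odds ratio (0.10/0.90)/(0.05/0.95) = 2.11.

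The bias passes the ±1-point target once the odds ratio for CB-PTSD, non-responders against responders, exceeds about 1.54. The formula works in both directions: with q = 2.5%, 0.6 × 5% + 0.4 × 2.5% = 4.0%, and the estimate is 1 point too high.

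**5. What the available data could recover.**
- At 60% of 2785, 2785 − 1671 = 1114 mothers lack the outcome.
- If every 2-month responder had started the baseline questionnaire, 2337 − 1671 = 666 of the missers started it, and the other 2785 − 2337 = 448 did not.
- If 20% to 40% of the 666 return (assumed), that is 133 to 266 mothers, or 133/1114 = 12% to 266/1114 = 24% of the missers.
- Take the best case for these returners: their 2-month status is recovered without error, they are typical of missers, and everyone else is still represented by responders. A 2.0-point bias then falls by 0.24 to 0.48 points, to about 1.8 to 1.5.

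Real recovery would be poorer, because returners supply correlated scores and not the City Birth Trauma Scale. Baseline scores add a further correction for missers who started that questionnaire, but its size cannot be computed from the documents.

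**The case against.** **Condensed article.** An article need not describe the handling of returners or each sensitivity analysis. That is right, and their absence is not the point here. But the article does state the response model's predictors and how they are used, and that stated choice leaves symptom-related non-response uncorrected.

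**Later data discarded?** A reader might infer that scores given at 6 and 12 months are thrown away. The document does not support this. It does not say how returners are handled, it leaves sensitivity analyses open, and later EPDS scores serve the second objective. What can be said is that no use in the primary estimate is stated.

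**Later answers the only evidence?** A reader might also infer that returners' answers are the only information on missers after 2 months. They are not. Hospital linkage, for mothers who consent to it, runs to 1 year after birth whether or not they answer. Baseline EPDS, PDEQ and QACE can also partly detect and correct a difference.

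**Direction.** The Introduction speaks of disengagement from care and weaker help-seeking, not of skipped research questionnaires. An underestimate is plausible but not established. The limitations box mentions loss to follow-up, though as a matter of data completeness and not as a possible bias in prevalence.

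**Limits of the remedy.** Imputation learned in responders assumes that their link between other scores and 2-month CB-PTSD also holds in missers, and the most avoidant parents may be the least likely to return. Both limits stand. They make the added analysis a check with partial correction, not a replacement for the planned estimate.

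**Conclusion.** The point holds in this form: the stated weights assume that 2-month response is unrelated to CB-PTSD given background, institution and parity-type variables. That fits poorly with the protocol's own description of the disorder, and symptom data able to test the assumption have no stated part in the primary estimate.

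The size is conditional. With 60% follow-up, 5% prevalence in responders, 7.5% to 10% in non-responders (assumed) and weights that explain none of the gap, the estimate is 1 to 2 points low, one to two times the planned margin. The documents do not show that such a gap exists. This should be addressed before the prevalence is reported, but it does not invalidate the design.

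**What to change.** Keep the planned weighted estimate and prespecify one companion analysis before 2-month results are seen, separately for mothers and co-parents.

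- **(a) Compare.** Set 2-month responders against missers on baseline EPDS, PDEQ and QACE and, for returners, on 6-month EPDS and PSS-4. Print this next to the prevalence.
- **(b) Re-estimate.** Multiply impute 2-month CB-PTSD status from baseline symptom and birth-experience measures plus any 6- and 12-month EPDS/EPDS-3A, PSS-4 and WHO-5. For parents with no later data, use weights whose response model includes the baseline symptom measures.
- **(c) Report.** If missers score worse, give both estimates and limit the wording of the national prevalence claim.

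**Cost.** Analysis-plan text and one extra analysis, with no new data collection. The part using later waves is available only after them. The imputation carries the responder-to-misser assumption named above. Parents who never started the baseline questionnaire have no baseline scores to use. Because returners are an unknown minority without a CB-PTSD scale, remaining symptom-dependent non-response cannot be ruled out, and the report should say so.

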### Patient and public involvement

Patient and public partners were involved in the development of this study. The protocol was reviewed by *Santé sexuelle Suisse,* the Swiss umbrella organisation for sexual health counselling centres and sex education services, and by *Periparto*, a national non-profit organisation dedicated to perinatal mental health. Representatives from these organisations participated in the Steering Committee responsible for validating the study questionnaires. In addition, the questionnaires were pre-tested with a panel of young parents from diverse backgrounds, and revised based on their feedback to improve clarity, relevance and acceptability, especially for sensitive topics related to mental health, sexuality, parenting and family life. In response to this feedback, the questionnaires were refined to better capture the co-parent’s perceived role, time spent as a couple and time for oneself. During data collection, free-text comments from participants in the baseline questionnaire were also reviewed to identify recurrent concerns. These comments informed the development of follow-up questionnaires, including items on perceived pressure or judgement regarding parenting choices. This process helped ensure that participant perspectives were reflected in the content of the instruments. To support participants during data collection, each questionnaire includes a message encouraging those experiencing distress to seek help from their midwife or specialised support services. This includes the 24/7 anonymous helpline *Heart2Heart* (www.143.ch).

## Ethics and dissemination

The SOCRATES study is conducted in accordance with the Swiss Human Research Act and the Declaration of Helsinki. Ethical approval has been obtained from the relevant cantonal ethics committees (number 2024-02262). All participants provided informed consent prior to data collection. Additional separate consent forms were requested for data linkage with hospital discharge records and recontact for optional future follow-up. Confidentiality is ensured through strict pseudonymisation procedures and secure data management systems.

Dissemination will include original research articles across midwifery, obstetrics, psychiatry and public health disciplines, targeting high-impact, open-access journals. Findings will be presented at international and national conferences and shared through professional journals in French, German and Italian to enhance accessibility among midwives and other clinicians. A scientific communication project has been submitted for funding to disseminate the project’s results to the broader public, targeting especially parents and their close circles.
